## Study outcomes

This study aims to evaluate the effect of a CBI strategy on clinical parameters, health literacy, medication adherence, and quality of life among individuals with both diabetes and hypertension. Data will be collected using structured and standardized instruments to ensure reliability and validity. Participants’ sociodemographic and clinical profiles will be recorded at baseline using a structured form to capture demographic details and health-related history.

### Clinical outcome

Clinical outcomes will include blood pressure and blood sugar levels. Blood pressure will be measured using a calibrated digital sphygmomanometer, with two readings taken and averaged to ensure accuracy. Blood glucose levels will be measured through random blood sugar test using a standardized glucometer. These measurements will be collected at baseline, 2 months, 3 months, and 6 months to track changes over time.

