## Aim of the study

The primary aim of the study is to evaluate the effectiveness of a CBI that integrates yoga practices, health education, dietary counseling, regular follow-up, and structured monitoring in improving clinical outcomes (blood pressure and blood sugar control) and health literacy among individuals with coexisting diabetes and hypertension.

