## Intervention group

Participants in the intervention group will receive a structured Community-Based Intervention (CBI) in addition to standard medical care. The CBI is designed to provide holistic care by integrating education, yoga-based lifestyle modification, and home-based monitoring. The intervention will be delivered in groups of 8–10 participants, led by the same trained nurse facilitator throughout the study, with support from a certified yoga instructor for yoga sessions. The complete intervention will span 6 weeks, with sessions conducted six days per week.

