### Home-Based monitoring and follow-up reinforcement

To strengthen continuity of care, participants will be trained in home-based monitoring of blood pressure and blood glucose and will maintain a lifestyle diary documenting daily yoga practice, diet, and medication adherence. The nurse will provide follow-up reinforcement through weekly contacts in the first month and biweekly thereafter, conducted via home visits or telephone calls. During these interactions, the nurse will review self-monitoring records, reinforce educational content, troubleshoot difficulties, and provide motivational support. Participants who show poor adherence or worsening clinical indicators will receive additional counseling and relate to peer support strategies to encourage engagement and compliance.

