## Control arm

Participants randomized to the control group will continue to receive routine medical care as prescribed by their physician. This care will include regular consultations with a physician, prescribed medications, routine monitoring of blood pressure and blood glucose, and general guidance on diet, physical activity, and lifestyle management. The control group will not receive any additional interventions, such as educational sessions, yoga-based activities, or nurse-led counseling. This design provides a clear comparator for assessing the effectiveness of the structured community-based intervention delivered to the experimental group.

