### Follow-Up and data collection procedures

Follow-up questionnaires and clinical measurements will be administered through in-person home visits to ensure convenience and maximize participation. Participants will complete self-report at their homes, guided by trained research staff to ensure accurate and complete responses. Clinical measurements, including blood pressure and blood glucose monitoring, will also be conducted during home visits. To promote adherence to scheduled assessments and minimize loss to follow-up, participants will receive prior reminders through telephone calls and text messages. The researcher, with support from local ASHA workers, will maintain regular contact with participants to reinforce the importance of completing each assessment and provide support for any challenges. Flexible scheduling of visits, tailored to participants’ availability, will further enhance compliance. Home visits will be conducted for participants unable to attend community sessions, ensuring continuity of data collection and minimizing attrition.

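### Half the weight of the blood pressure outcome rests on the first reading, and only the intervention arm is trained in home measurement, so a small bias towards the intervention is possible and cheap to remove

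*Protocol article*

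**What the plan says.** The Clinical outcome section of the protocol article states the rule: "Blood pressure will be measured using a calibrated digital sphygmomanometer, with two readings taken and averaged to ensure accuracy". It applies at baseline and at 2, 3 and 6 months. No reading is dropped. Blood pressure is part of the primary aim, which is stated as "improving clinical outcomes (blood pressure and blood sugar control) and health literacy".

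The intervention is described as "integrating education, yoga-based lifestyle modification, and home-based monitoring", and under it "participants will be trained in home-based monitoring of blood pressure and blood glucose and will maintain a lifestyle diary". The nurse reviews these self-monitoring records at regular contacts.

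Of the comparator, the Control arm section says: "The control group will not receive any additional interventions, such as educational sessions, yoga-based activities, or nurse-led counseling". Usual care for controls nevertheless includes "routine monitoring of blood pressure and blood glucose, and general guidance on diet, physical activity, and lifestyle management".

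The outcome readings are taken at home in both arms: "Clinical measurements, including blood pressure and blood glucose monitoring, will also be conducted during home visits". The Limitations section says that the trial is unblinded and that data are collected by staff outside the intervention. It does not mention unequal practice in blood pressure measurement.

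**The concern.** A first reading can include a short-lived reaction to being measured. Averaging it with a second reading reduces random error, which is the purpose the article gives, but it leaves half of any systematic first-reading excess in the outcome.

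If that excess were equal in both arms it would cancel in the comparison. Here the arms differ after randomization in how much practice they have with measurement, because trained home monitoring goes to one arm only. Neither randomization nor the baseline reading removes a difference that arises later. It can recur at each follow-up visit, and its likely direction is in favour of the intervention. In a two-reading mean it cannot be told apart from a true fall in blood pressure, which is a primary-aim outcome.

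**Working it through.** **1. The plan's own sample size.** The inputs in the Sample size section are SD 0.74, difference 0.40, and z-values 1.96 and 0.84.

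n per group = 2 × (0.74 × 2.80 / 0.40)² = 53.7, so 54. With 10% attrition, 54 / 0.9 = 60.

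The stated figures reproduce. The unit and outcome behind 0.74 and 0.40 are not named, so they give no blood pressure SD in mmHg. Only the 54 per arm is carried forward.

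**2. Bias in the two-reading mean.** Let e be the first-reading excess in controls, and f the share of it that is lost in the intervention arm but not in controls. The second reading is taken as free of the reaction.

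Bias = 0.5 × e × f

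The documents give neither e nor f. I assume e = 2 to 6 mmHg and f = 0 to 1. Zero is included because controls are also measured regularly.

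- f = 0: bias 0 for any e
- f = 0.5: 0.5 × 2 × 0.5 = 0.5 mmHg, up to 0.5 × 6 × 0.5 = 1.5 mmHg
- f = 1: 0.5 × 2 × 1 = 1 mmHg, up to 0.5 × 6 × 1 = 3 mmHg

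**3. Effect on the error rate.** For one unadjusted two-sided comparison at one visit, with no true effect:

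SE = SD × √(2/54)

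P(reject) = 1 − Φ(1.96 − b/SE) + Φ(−1.96 − b/SE)

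The systolic SD is also an assumption: 15 mmHg, with 12 and 18 for the range.

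| Bias b (mmHg) | SD 12 (SE 2.31) | SD 15 (SE 2.89) | SD 18 (SE 3.46) |
|---|---|---|---|
| 0 | 5.0% | 5.0% | 5.0% |
| 0.5 | 5.5% | 5.3% | 5.2% |
| 1 | 7.2% | 6.4% | 6.0% |
| 2 | 13.9% | 10.7% | 8.9% |
| 3 | 25.5% | 18.0% | 13.9% |

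**4. Scale.** At SD 15 the difference detectable with 80% power is 2.80 × 2.89 = 8.1 mmHg. A bias of 0.5 mmHg is about 6% of that, and 3 mmHg about 37%.

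**5. After the change.** If the first reading is left out of the mean, a gap confined to that reading contributes 0 instead of half its size. Any gap still present at later readings stays. The sample size is unaffected.

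**The case against.** The strongest counter-argument is that controls are far from new to the cuff. Eligibility requires both diagnoses for at least a year and current treatment. Usual care includes routine blood pressure checks, and controls have the same study readings at every visit. The readings are taken in participants' own homes, under one stated procedure, by staff outside the intervention, so the intervention arm gains no familiarity with the assessor. Nothing in the documents shows that self-measurement dampens the reaction to being measured by someone else. All of this stands. It narrows the likely gap and makes the upper end of the range unlikely, but it does not make practice equal in the two arms.

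The error rates come from a single unadjusted comparison, whereas the article plans t-tests and repeated measures ANOVA with adjustment for multiple comparisons. That also stands, so the percentages show scale and do not predict the trial's error rate. Adjusting for multiplicity would not remove a bias.

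Yoga and relaxation are meant to lower stress, so a calmer first reading could be partly an intended effect. This is fair, and the documents cannot separate the two.

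Averaging two readings contradicts nothing in the article, and details such as a rest period may be left to a fuller procedure. The absence of a rest period is therefore no part of this point. The averaging rule itself is stated, and the point concerns that rule.

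A reader might go further and infer that controls are unused to measurement, or that the blood pressure result is bound to be biased. The documents do not support either. They describe routinely monitored controls and give no evidence that a first-reading reaction occurs in this population.

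**Conclusion.** The point holds as a minor one. The stated rule gives the first reading half the weight, and trained home measurement is confined to one arm. A somewhat smaller first-reading reaction in the intervention arm is therefore possible, and it would favour that arm.

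On the assumed excess of 2 to 6 mmHg and a differential loss of 0 to 100%, the bias is 0 to 3 mmHg. At SD 15 mmHg with 54 per arm, the 5% error of a single comparison becomes 5% to 18%. The 18% needs a 6 mmHg excess kept in full by controls and lost in full by the intervention arm, so it is an outer bound and not an expectation. The excess, the loss and the SD are all assumptions. The point affects blood pressure only, not glucose or the questionnaires.

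**What to change.** In the Clinical outcome section, change the rule to three readings at every visit, baseline included, in both arms, with the mean of the last two as the outcome. Record all three values, and compare the first-minus-later difference between arms as a check. A smaller difference in the intervention arm would show that the reaction differs, though not whether practice or relaxation caused it.

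The cost is one more reading with the same device and staff, about two minutes per visit, and one line of text. No extra visits or participants are needed. The outcome is still a mean of two readings. The change removes only the part of the reaction confined to the first reading. It has to be made before the visits take place, because values not recorded then cannot be recovered at analysis.

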### Health literacy

Health literacy will be assessed using a modified Diabetes and Hypertension Health Literacy Scale, consisting of 14 items. This scale evaluates participants’ understanding of dietary habits, physical activity, and self-care practices for managing both conditions. The scale will be validated by 11 experts in the relevant fields, and reliability will be assessed with 10% of the total sample to ensure internal consistency. The scale was modified because existing instruments assessed diabetes and hypertension separately; the adapted version provides an integrated assessment suitable for participants with comorbid diabetes and hypertension. Health literacy assessments will be conducted at baseline, 2 months, 3 months, and 6 months.

### Medication adherence

Medication adherence will be measured using the standardized 8-item Morisky Medication Adherence Scale (MMAS-8), which evaluates various domains of medication-taking behavior in chronic disease management [20]. Assessments will occur at baseline, 2 months, 3 months, and 6 months, providing repeated measures to track adherence over time.

### Quality of life

Quality of life will be assessed using a modified questionnaire derived from the Diabetes Quality of Life Questionnaire (DQOL) and the High Blood Pressure Quality of Life Questionnaire (HBP-QLQ), consisting of 16 items covering physical, psychological, social, and environmental domains. The scale will be validated by 11 experts, and reliability will be assessed with 10 % of the sample to ensure internal consistency. Similar to the health literacy scale, this instrument was modified to integrate assessment of both diabetes and hypertension for accurate evaluation in participants with comorbid conditions. Assessments will be conducted at baseline, 2 months, 3 months, and 6 months. The complete participant assessment timeline is illustrated in the CONSORT diagram (Fig. 1).

**Fig. 1 fig0001:**
[figure not shown]
Participant timeline across various time points.

### Follow-Up and data collection procedures

Follow-up questionnaires and clinical measurements will be administered through in-person home visits to ensure convenience and maximize participation. Participants will complete self-report at their homes, guided by trained research staff to ensure accurate and complete responses. Clinical measurements, including blood pressure and blood glucose monitoring, will also be conducted during home visits. To promote adherence to scheduled assessments and minimize loss to follow-up, participants will receive prior reminders through telephone calls and text messages. The researcher, with support from local ASHA workers, will maintain regular contact with participants to reinforce the importance of completing each assessment and provide support for any challenges. Flexible scheduling of visits, tailored to participants’ availability, will further enhance compliance. Home visits will be conducted for participants unable to attend community sessions, ensuring continuity of data collection and minimizing attrition.

## Ethical considerations

The study received approval from the Institutional Ethics Committee (IEC) of the Institution (Reference No: IEC/IMS.SH/SOA/2022/433). The trial has been prospectively registered in the Clinical Trial Registry of India (CTRI/2024/08/071,775).

Informed consent will be obtained from all participants before enrolment. The consent form will be provided in both English and Odia to ensure participants fully understand the study procedures. To maintain confidentiality, personal information will not be shared with third parties. Data confidentiality and anonymity will be maintained strictly throughout all phases of the study, data collection, analysis, reporting, and publication.

## Protocol validation

The rising prevalence of coexisting diabetes and hypertension, particularly in underserved urban communities, presents significant challenges for effective disease management and long-term health outcomes [21]. Conventional care often focuses on pharmacological treatment alone, neglecting the role of lifestyle modification, patient education, and self-management support, which are critical for achieving optimal glycemic and blood pressure control [22,23]. Evidence suggests that structured community-based interventions, including health education, yoga-based lifestyle modification, dietary counseling, and regular monitoring, can improve treatment adherence, enhance health literacy, and positively influence quality of life [24,25]. However, there is limited rigorous evidence from randomized controlled trials in urban slum populations, where barriers such as low health literacy, limited access to care, and socioeconomic constraints may impede successful management [26,27]. Conducting this RCT will allow for a systematic evaluation of the effectiveness of a comprehensive CBI strategy compared to standard care. The study’s design, including block randomization, standardized outcome assessment, and follow-up at multiple time points, ensures methodological rigor and minimizes bias. Findings from this trial are expected to provide evidence-based guidance for implementing scalable, patient-centered interventions that integrate lifestyle, education, and clinical care, thereby addressing the gap in chronic disease management within vulnerable populations.

To the best of our knowledge, this protocol is novel and has not been implemented in any prior settings; therefore, no preliminary data are currently available.

## Limitations

This randomized controlled trial has several limitations. First, it is conducted in selected urban slums, which may limit generalizability to rural areas or populations with higher socioeconomic status. Participants’ sociodemographic profiles will be documented to provide contextual interpretation of the findings. Second, blinding is not employed, and participants are aware of their group allocation, which may introduce performance bias, particularly in self-reported outcomes. To mitigate this, validated assessment tools will be used, and data will be collected by trained personnel who are not involved in the intervention. Third, the intervention relies on participants’ attendance at yoga and counseling sessions, as well as adherence to home-based monitoring. Variations in participation may influence outcomes; therefore, reminder calls, motivational support, and flexible scheduling will be implemented to enhance adherence. Fourth, potential confounding factors such as concurrent treatments, dietary changes, or lifestyle modifications cannot be fully controlled. Baseline assessments and ongoing monitoring will help account for these factors during analysis.

Additionally, given the study’s focus on urban slum populations, access to regular healthcare and diagnostic services may be limited. This could lead to underdiagnosis or delayed identification of chronic conditions, affecting the representativeness of the recruited sample. Consequently, the findings are most generalizable to similar urban, resource-constrained communities rather than broader urban or rural populations. Nevertheless, by leveraging existing public health infrastructure, including urban primary health centers, NCD registers, and frontline health workers, the study reflects real-world conditions and aims to generate contextually relevant evidence that can inform scalable community-based interventions in comparable low-resource settings.

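### Post-baseline outcome assessors are left unmasked although they already stand outside the intervention, so avoidable detection bias can enter the staff-guided scales

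*Protocol article*

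**What the plan says.** On blinding, the Limitations section says that "blinding is not employed, and participants are aware of their group allocation, which may introduce performance bias, particularly in self-reported outcomes". The remedy it offers is that "validated assessment tools will be used, and data will be collected by trained personnel who are not involved in the intervention". No other section masks outcome assessors or mentions bias arising from what they know.

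On how outcomes are gathered, the section on follow-up and data collection says: "Participants will complete self-report at their homes, guided by trained research staff to ensure accurate and complete responses". It adds: "Clinical measurements, including blood pressure and blood glucose monitoring, will also be conducted during home visits". Under Clinical outcome, blood pressure is "measured using a calibrated digital sphygmomanometer, with two readings taken and averaged to ensure accuracy", and glucose is a random reading by glucometer.

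Health literacy belongs to the primary aim (Aim of the study), alongside blood pressure and blood sugar. The literacy scale is a modified 14-item instrument, of which the article says: "The scale will be validated by 11 experts in the relevant fields". The modified quality-of-life questionnaire has a similar plan. The Protocol validation section nevertheless presents the design as one that keeps bias to a minimum.

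**The concern.** Participants, the nurse facilitator and the yoga instructor cannot be masked to a yoga and coaching programme. Outcome assessors are a different matter. Taking no part in delivery is not the same as not knowing the allocation, and the article secures only the first.

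An assessor who knows the arm may explain an item more fully, prompt, or read an unclear answer more kindly in one arm than in the other. This is detection bias. The Limitations section names only performance bias, which comes from participants' awareness. A validated tool does not stop a person who knows the arm from influencing how it is answered.

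At stake is the between-arm comparison on health literacy, medication adherence and quality of life. A systematic shift of this kind does not shrink as the sample grows.

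**Working it through.** **1. Who could be masked, and when.**
- Baseline: the data collection plan places baseline assessment before allocation, so there is no arm to know. The exposure is confined to 2, 3 and 6 months.
- Follow-up: the Limitations section says collectors are not involved in the intervention, so masking them needs no new staff.
- Two passages blur this separation. The intervention section has the nurse facilitator conduct a baseline assessment. The ASHAs (community health workers) who motivate intervention participants also support contact around follow-up assessments. These roles should be reconciled with the Limitations statement.

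**2. Which outcomes are exposed.**
- Most exposed: the three scales, where staff are present and "guided by trained research staff to ensure accurate and complete responses".
- Less exposed: blood pressure (digital device, fixed two-reading rule, averaged) and glucose (glucometer). Some room remains for glucose, because a random reading depends on when it is taken and the article states: "Flexible scheduling of visits, tailored to participants’ availability, will further enhance compliance".

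**3. The plan's own figure.** Inputs from Sample size: SD 0.74, difference 0.40, z-values 1.96 and 0.84, attrition 10%.

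n per group = 2 × 0.74² × (1.96 + 0.84)² / 0.40² = 2 × 0.5476 × 7.84 / 0.16 = 53.66, rounded up to 54. Then 54 / 0.90 = 60 per group, 120 in total. The stated figures reproduce, and masking assessors does not alter them.

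**4. Illustration of what a shift would do.** Suppose there is no true effect and assessor influence alone moves the difference in means by b. The article gives no value for b, so the values below are assumptions.

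SE = 0.74 × √(2/54) = 0.142

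False-positive rate = P(Z > 1.96 − b/SE) + P(Z < −1.96 − b/SE)

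| Assumed b | Share of planned 0.40 | b/SE | Two-sided false-positive rate |
|---|---|---|---|
| 0 | 0% | 0 | 5.0% |
| 0.05 | 12.5% | 0.35 | 6.4% |
| 0.10 | 25% | 0.70 | 10.8% |
| 0.15 | 37.5% | 1.05 | 18.4% |
| 0.20 | 50% | 1.40 | 29.0% |

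The sample size section does not name the outcome behind 0.74 and 0.40, so the table shows sensitivity on the planning scale. It is not an estimate for health literacy or any other named outcome.

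**The case against.** The case on the other side has several parts.

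- **The limitation is disclosed and mitigated.** Lack of blinding is stated openly. Collectors outside the intervention have less stake in the result, and the article adds two days of training in standardised data collection, supervision and random checks. This stands as partial mitigation, so a reader who infers that the plan does nothing about assessor influence goes too far. What remains is that none of these measures keeps the allocation from the assessor.
- **The measurements are objective.** This stands in large part for blood pressure and glucose. A reader might infer that all primary-aim outcomes are equally exposed, but the devices and the two-reading rule do not support that.
- **The scales are self-completed.** The article describes guided self-completion at follow-up and mentions structured interviews only for baseline. It does not say that staff supply or record the answers. Guidance is still a route for influence.
- **Aware participants bias self-report in any case.** True, and masking assessors cannot remove it. How much masking would add cannot be known from the document. That is no reason to leave a second source in place.
- **Home visits will unmask some assessors.** Likely, since intervention participants attend local sessions and keep diaries. This argues for masking as far as possible, with a record of failures, rather than a promise of full masking.
- **The scales will be validated.** Expert validation and reliability testing are planned, so the statement that validated tools will be used is not contradicted. The point is only that validation does not cure detection bias.

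**Conclusion.** The concern holds in a limited form. The article makes a stated choice to use no blinding and leaves post-baseline assessors unmasked where masking is at least partly feasible. The exposure lies mainly in the three staff-guided scales at 2, 3 and 6 months, one of which (health literacy) serves the primary aim. It is smaller for the device readings and absent at baseline, provided baseline precedes allocation as planned.

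A shift in favour of the intervention is the likely direction, but that is a judgement; the documents give no evidence of direction or size. The range of 6.4% to 29.0% rests on assumed shifts of 0.05 to 0.20, an unnamed outcome with SD 0.74, 54 per arm and no true effect. A reader might take it as this trial's actual error rate, and the documents do not support that. The recommendation rests on masking being cheap and feasible, not on any one row of the table.

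**What to change.** In Limitations, state that participants and facilitators are unblinded and that post-baseline outcome assessors are masked to allocation as far as possible. Name detection bias as a limitation, and do not offer validated tools as its remedy.

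In the section on follow-up and data collection:
- give assessors no allocation list and no intervention records;
- keep ASHAs who motivate intervention participants out of outcome assessment;
- use one arm-neutral reminder script that asks all participants not to reveal their group;
- present scale items in the same standardised wording, with the same scripted clarifications, in both arms, so that participants with low health literacy still get help;
- have assessors record after each visit whether they learned the arm.

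The cost is protocol wording, an item in the existing two-day training, a line in the existing reminder call and one recorded item per visit. Sample size, visit schedule and staff numbers need not change, although ASHA roles around follow-up must be set out. The downside is that some assessors will still be unmasked at home visits, which the record will show, and that self-report bias from participants who know their arm remains.
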